### Implementation moderators

​​ In Aim 2, we will use the Consolidated Framework for Implementation Research (CFIR) [65, 66] to examine center-level implementation determinants at the inner setting (e.g., prior experience with EBPs), outer setting (e.g., local SGM policy climate, mental health workforce), intervention characteristics (e.g., attitude towards EBP), individual characteristics (e.g., staff turnover, client demographics), and implementation process (e.g., implementation barriers and facilitators) (see Table 1). Surveys and interviews with center directors and providers from baseline and 4-, 8-, 12-, and 24-month follow-up periods will provide data to inform whether CFIR-informed center-level determinants moderate these outcomes.

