Maintenance	∙ Funding stability, environmental support, organizational capacity, and strategic planning will be measured by the Program Sustainability Assessment Tool [123] and semi-structured qualitative interviews with providers and directors.	Director surveys, provider surveys and qualitative interviews	4 m, 8 m, 12 m 24 m
Implementation determinants			
Inner setting	∙ Motivation for change, resources, and staff attributes will be measured by subscales of the Organizational Readiness for Change– Treatment Staff Version and Organizational Readiness for Change– Treatment Director Version [124].	Director surveys, provider surveys	baseline, 4 m, 24 m
Outer setting	∙ SGM Policy Climate (e.g., anti-LGBTQ laws/policies) will come from existing policy and attitudinal indices [35, 55, 125] linked to the municipality of each center. ∙ Community socioeconomic disadvantage and rurality (e.g., poverty, housing characteristics, unemployment, education) will come from the American Community Survey [126] and be linked to the county of each center. ∙ Mental health workforce characteristics (e.g., provider prevalence in each state, continuing education requirements of centers’ states) will derive from existing metrics [127]. ∙ Semi-structured qualitative interviews with providers and directors will inform assessment of the outer setting.	Secondary data, provider and director qualitative interviews	baseline
Intervention characteristics	∙ Directors’ and providers’ openness to adopting EBPs and perceived divergence between EBPs and current practice will come from the EBP Attitude Scale [128].	Director and provider surveys	baseline, 4 m, 24 m
Individual characteristics	∙ Provider, director, and client demographics (e.g., race/ethnicity, sexual orientation, gender) will be assessed via self-report questionnaires.	Provider, director, and client surveys	baseline, 4 m, 8 m, 12 m 24 m

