Implementation process	∙ Implementation barriers and facilitators will come from interviews about staff planning, engagement, and execution, and other feedback on the implementation process [129]. ∙ Perceived appropriateness of the intervention and implementation strategy will be assessed with the Training and Adoption Barriers Scale [130] and the Intervention Appropriateness Measure [131]. ∙ Training engagement and satisfaction will be assessed via questionnaires designed for this study and an adapted version of the Client Satisfaction Questionnaire [132].	Director, provider, and supervisor qualitative interviews	4 m, 8 m, 12 m, 24 m
Implementation mechanisms			
Organization-level implementation targets	∙ Organizational norms of importance, expectations, and rewards of implementing LGBTQ-affirmative CBT will be measured with the Focus, Recognition, and Rewards subscales of the Implementation Climate Scale [133]. ∙ Organizational policies and communications about LGBTQ-affirmative CBT will be assessed with the Implementation Leadership Scale [134]. ∙ Supervision competency will be measured by the Supervision Evaluation and Supervisor Competence Scale [135].	Director, provider, and supervisor surveys	baseline, 4 m, 8 m, 12 m, 24 m
Provider-level implementation targets	∙ Provider LGBTQ-affirmative CBT competency will be measured using the LGBTQ-affirmative CBT Knowledge Scale [57]. ∙ Provider motivation to implement LGBTQ-affirmative CBT will be measured with the adapted Measure of Innovation-Specific Implementation Intentions [136]. ∙ Providers’ LGBTQ counseling competency will be assessed with the skills subscale of the Sexual Orientation Provider Competency Scale [137]. ∙ Providers’ familiarity and experience with case conceptualization will be assessed by a seven-item questionnaire developed for this study.	Provider surveys	baseline, 4 m, 8 m, 12 m, 24 m
	∙ Clients’ perceived therapeutic alliance will be measured with the Working Alliance Inventory [114]. ∙ Clients’ perceptions of therapist efficacy in LGBTQ-affirmative CBT skills will be assessed with the adapted Sexual Orientation Counselor Competency Scale [113].	Client surveys	baseline, 4 m, 8 m, 12 m, 24
Effectiveness outcomes			

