#### Moderation analyses

To identify center- and provider-level determinants of implementation success, we will use stepwise regression [97], using 8-month simulated practice skills assessment of implementation fidelity as the primary outcome. Stepwise regression will iteratively add and remove each of the implementation determinants described previously and their interaction with implementation strategy to identify the subset of determinants with the minimal Akaike information criterion (AIC) [98]. We will re-run this analysis with each of the secondary implementation outcomes.

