### Dissemination

The final trial dataset will be available to all study investigators. Deidentified data for participants who have agreed to have their data shared will be submitted to the National Institutes of Mental Health Data Archive. In addition, the data and statistical code will be available by request to qualified researchers. To ensure that results of this research increase the likelihood that SGM individuals nationwide receive LGBTQ-affirmative CBT — one of the only EBPs developed to address SGM individuals’ mental health — and therefore have the strongest possible effect on SGM mental health disparities, we have planned for six months of dissemination activities. We will first present results to a community advisory board (CAB) of 12 directors, providers, and SGM community members to gain interpretive feedback and suggestions for dissemination activities. We will then summarize study results in an accessible research brief and accompanying webinar for all LGBTQ community center directors nationwide.

The brief and webinar content, which the CAB will review and shape, will identify the most effective implementation strategies for a variety of center-level conditions and specify barriers and facilitators of successful implementation so that center directors and providers can select implementation strategies accordingly. Alongside these results, we will instruct centers on how to access all implementation materials (i.e., for providers, supervisors, and clients) through our training platform. This dissemination phase will also allow us to explore centers’ maintenance or discontinuation of implementation strategies through exploratory interviews with directors and providers at centers representing diverse geographies, budgets, and staff and client makeup. These activities will inform future planning and needed supports on the part of community organizations, funders, and academic researchers to ensure that SGM continue to benefit from this and any future EBP capable of reaching SGM individuals across high-need, low-resource settings.

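### The Aim 2 moderator model admits determinants measured after randomization, including process measures with no baseline value, and selects them by AIC without error control, yet its results are to guide centers' choice of strategy

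*Protocol article*

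**What the plan says.** All of this is in the protocol article.

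- **Implementation moderators.** The determinant domains are inner setting, outer setting, intervention characteristics, individual characteristics and "implementation process (e.g., implementation barriers and facilitators) (see Table 1". On timing: "Surveys and interviews with center directors and providers from baseline and 4-, 8-, 12-, and 24-month follow-up periods will provide data to inform whether" these determinants moderate the outcomes.
- **Table 1, implementation process row.** It covers barriers and facilitators, perceived appropriateness, and engagement: "Training engagement and satisfaction will be assessed via questionnaires designed for this study". The listed time points are 4, 8, 12 and 24 months, with no baseline.
- **Table 1, inner setting and intervention characteristics rows** (readiness for change, attitudes to evidence-based practice). The time points are "baseline, 4 m, 24 m".
- **Moderation analyses.** The outcome is set by "using 8-month simulated practice skills assessment of implementation fidelity as the primary outcome". The candidate set is: "Stepwise regression will iteratively add and remove each of the implementation determinants described previously and their interaction with implementation strategy". The rule is to "identify the subset of determinants with the minimal Akaike information criterion (AIC". The search is repeated for each secondary implementation outcome.
- **Dissemination.** The brief and webinar for center directors "will identify the most effective implementation strategies for a variety of center-level conditions", so that directors and providers can choose accordingly.

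**The concern.** A moderator answers a question asked before the strategy is chosen: in which kind of center does a given strategy work better? Only characteristics that the strategy has not altered can answer it. Engagement with training, satisfaction with it and perceived appropriateness of the strategy refer to a different package in each arm. They are results of allocation. Conditioning on them, or interacting them with strategy, distorts the strategy contrast inside that model, and a director choosing a strategy could not know their values in advance.

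The second issue is selection. AIC is a prediction criterion with a lenient implied significance level. It is applied here to every determinant and every interaction with a three-level strategy, then again for each secondary outcome. No error control or validation is stated.

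At stake is the advice to low-resource centers on which strategy suits them. Some of that advice could rest on chance or on consequences of the training.

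**Working it through.** **1. Time order, from the text**

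| Determinant domain | When measured (Table 1) | Usable as a moderator of 8-month fidelity? |
|---|---|---|
| Outer setting | baseline; indices from secondary data | yes |
| Inner setting, practice attitudes | baseline, 4, 24 months | baseline value only; the 24-month value follows the outcome |
| Demographics | baseline and all follow-ups | baseline value only |
| Implementation process | 4, 8, 12, 24 months | no: there is no baseline value |

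The Moderation analyses section does not say which wave enters. By contrast, the Mediation analyses section fixes the order explicitly, with 4-month targets for the 8-month fidelity outcome.

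Baseline is not wholly clean either. Director nomination and provider registration follow randomization (Participants), and participants are unmasked (Randomization). Secondary data and director reports gathered before allocation are not exposed to this.

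**2. The plan's own figures**

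No power or error figure is given for the moderator analysis. The Aim 1 sample size section supplies the inputs: 90 centers, about 6 providers each (180 per arm), ICC up to 0.1. As a check on those inputs:

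- Standardized change: 0.14/√0.0439 = 0.67, as stated.
- Detectable effect: d = (z for two-sided 0.025 + z for 80% power) × √(2·DE/180), with DE the design effect and two-sidedness assumed. This gives 0.333 at ICC 0.01 (0.340 with t on 58 df) and 0.398 at ICC 0.1 (0.407 with t).
- The lower end of the stated 0.34–0.46 reproduces. The upper end needs an allowance that is not stated, such as attrition of about 30–35%. The stated range is therefore conservative and is not at issue here.

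**3. Error rate implied by minimum AIC**

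A term with q degrees of freedom lowers AIC when its chi-square exceeds 2q.

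- Main effect, 1 df: P(χ²₁ > 2) = 0.157.
- Interaction with strategy, 2 df: P(χ²₂ > 4) = e⁻² = 0.135.
- If clustering were ignored at ICC 0.1: DE = 1 + (6 − 1) × 0.1 = 1.5, and for a center-level determinant P(χ²₂ > 4/1.5) = 0.264.

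**4. At least one false interaction among K null determinants**

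K is not stated. Table 1 suggests about 17, so 10 to 25 is shown as an assumption.

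Treating the tests as independent, with clustering handled, 1 − (1 − 0.135)^K gives 0.77, 0.92 and 0.97 for K = 10, 17 and 25.

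Two-way AIC stepwise was then simulated under a global null: 90 centers × 6 providers, ICC 0.1, independent center-level determinants, full retention, starting from strategy alone, with 600, 400 and 200 runs for the three values of K. Clustering was handled by analyzing center means.

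| Entry rule | Clustering | K = 10 | K = 17 | K = 25 |
|---|---|---|---|---|
| Interactions enter freely | handled | 0.77 | 0.91 | 0.99 |
| Interactions enter freely | ignored | 0.91 | 0.97 | 1.00 |
| Only after the main effect | handled | 0.27 | 0.40 | 0.59 |
| Only after the main effect | ignored | 0.48 | 0.69 | 0.81 |

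The main-effect-first rows depend on the starting model. In a smaller run that began from the full model under the same rule, with clustering handled, the chance was 0.87 at K = 10 and 1.00 at K = 17. The plan states neither the entry rule nor the starting model.

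**5. A determinant measured after the outcome**

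Suppose a 12- or 24-month center measure has no effect on fidelity but reflects it with correlation 0.3 (an assumption). It is selected in 93% of simulated trials, against 25% at zero correlation. If the correlation differs by arm (0, 0.25, 0.5), a false interaction with strategy is selected in 61%, against about 10% at zero correlation.

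**The case against.** The strongest reply has five parts.

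- **The center effect.** A reader might infer that the moderator model has none, because none is named. The documents do not support that. The section is silent in a condensed article, and the other models (provider fidelity, effectiveness, mediation) all name center as a random effect. The clustering-ignored rows above are conditional illustrations only.
- **Near certainty.** A reader might also infer that false moderators are near certain. That requires free entry or a full-model start, together with many null determinants or ignored clustering. Under the mildest rule examined the chance is 0.27. Moreover, the section covers provider-level as well as center-level determinants, so a design effect of 1.5 would not apply to every candidate.
- **Waves after 8 months.** The later waves under Implementation moderators may be meant partly as outcome data, since outcomes run to 24 months. Use of 12- or 24-month determinants for the 8-month outcome is permitted by the text, not stated.
- **Process data.** The Table 1 data source for that row is qualitative interviews. That may keep barriers and facilitators out of a regression, but the row also holds questionnaire scales for appropriateness, engagement and satisfaction.
- **Consequences.** This is a secondary aim, and a community advisory board reviews and shapes the brief. That review is useful, but it cannot detect a chance interaction.

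These points limit the size of the problem. They do not supply a baseline value for the process domain or a wave rule for the rest. Deferring to a later analysis plan does not settle it either, because the article already fixes the candidate set, the outcome time and the selection criterion.

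**Conclusion.** The concern holds in this form. As written, Aim 2 would treat consequences of the strategy as its moderators, and it does not exclude determinant values that follow the 8-month outcome. The selection rule admits a null interaction with strategy 13.5% of the time, or about 26% for a center-level determinant if clustering at ICC 0.1 were ignored. With clustering handled, the chance of at least one false strategy interaction is about 0.77–0.99 under free entry. It is about 0.27–0.59 under main-effect-first entry from the strategy-only model.

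These figures assume 10–25 determinants, all null, independent and at center level, with full retention. The timing defect needs none of these assumptions.

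A reader might also infer that the trial's main result is biased. It is not: the primary Aim 1 model contains time, strategy by time, and random effects, with no determinants.

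**What to change.** 1. State that candidate moderators are baseline values and fixed secondary data only. Note that baseline surveys follow unmasked allocation, so outer-setting data and director reports collected before randomization are the cleanest.
2. Move the process scales and all follow-up values to the mediation analysis or to description.
3. State that the moderator model carries the center random effect used in the provider fidelity model.
4. State the starting model and whether an interaction may enter only after its main effect.
5. Either add multiplicity control (Holm or false-discovery rate on the interaction tests) or validation that leaves out whole centers, or label the selected moderators exploratory in the brief and webinar.

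The cost is wording plus a modest amount of analysis. No new data are needed. The downside is that fewer moderators will be declared.

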### Effectiveness outcomes

We will compare the three training strategies in terms of their impact on client mental health symptoms using reliable and valid brief symptom assessment measures. Primary effectiveness outcomes include symptoms of depression and suicidality [88] and secondary effectiveness outcomes include symptoms of anxiety [89] and substance use [90, 91]. We will also examine mediators of impact through the hypothesized target mechanisms of LGBTQ-affirmative CBT (e.g., internalized stigma) using reliable and valid assessments [92] using data collected at baseline and 4-, 8-, 12-, and 24-month follow-up periods (see Table 1).

### Implementation and effectiveness mediators

We will explore serial mediation of training strategies on implementation success and client mental health through organizational (e.g., shared norms of the importance of EBP) and provider (e.g., self-efficacy for EBP delivery) factors, drawing on theories of organizational [68, 69] and provider [70–73] change.

### Data collection, management, and analysis

Mental health provider, director, and local supervisor participants will complete baseline and follow-up surveys via Qualtrics. Client surveys will be administered and stored on REDCap. All participant consent, contact, tracking, and scheduling information will be recorded in REDCap.

#### Provider implementation fidelity outcome analyses

We will summarize provider characteristics (e.g., volunteer status, length of SGM service) overall and by implementation strategy and assess for baseline imbalances. We will then compare the implementation outcomes for the Materials Only condition vs. Direct Training vs. Local Supervision. The primary implementation outcome is provider implementation fidelity (assessed via simulated practice responses) at 8-month follow-up; secondary outcomes include 8-month provider self-efficacy, competency, familiarity, and use of LGBTQ-affirmative CBT. For primary and secondary outcomes, will use mixed effects models [93] with the identity link function to compare the effect of implementation strategies. The fixed effects include the time effect and the time × implementation strategies interaction terms; the random effects include center and within-provider repeated measures. We will use the robust score test to assess whether the interaction terms are significantly different across the three strategies, with a 0.05 overall Type I error rate, and a 0.025 error rate for each of the two primary strategy comparisons. For secondary outcomes, we will compare implementation strategies with a 0.05 Type I error rate. We will re-run these analyses with 12- and 24-month outcomes to determine implementation maintenance.

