We hypothesize that these three additive training implementation strategies will predict respective graduated increases in implementation success at 4-, 8-, 12-, and 24-months post-training (see Figs. 1 and [67]). That is, we predict that reach, effectiveness, adoption, implementation, and maintenance will be higher in the Local Supervision condition relative to the Direct Training condition and that the Direct Training condition’s implementation outcomes will be higher than the Materials Only condition. Drawing on theories of organizational [68, 69] and provider [70–73] change, we also hypothesize that organizational (e.g., shared norms of the importance of EBP) and provider (e.g., self-efficacy for EBP delivery) factors will mediate the stronger impact of the more intensive training strategies on implementation success and client mental health outcomes. To facilitate this latter aim, in a subset of 15 LGBTQ community centers (five centers per condition), we will compare the three training implementation strategies in terms of client mental health symptom change from before implementation to 4, 8, 12, and 24 months after.

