##### Sample size justification

Provider implementation fidelity serves as our primary outcome used to estimate sample size given its role in linking provider behavior to client mental health [84, 94–96]. We estimate that approximately six mental health providers will enroll per center, or about 540 providers total. Power was computed to test the null hypotheses of no difference between Materials Only and Direct Training and between Direct Training and Local Supervision in a cluster trial. For the primary implementation outcome, the change from baseline to 8-month follow-up was estimated as 0.14 for the Direct Training strategy and its variance was estimated as 0.0439 using data obtained from the waitlist-controlled trial [57]. Thus, the standardized change for the Direct Training strategy was estimated at 0.67. With a 0.025 Type I error rate, allowing for two primary comparisons between the three strategies, we will have 80% power to detect an effect of *d* = 0.34–0.46 on the 8-month change of the primary outcome, assuming a between-center ICC ≤ 0.1. In other words, we will have 80% power to detect the difference between Materials Only and Direct Training when the standardized change for Materials Only is ≤ 0.21–0.33, and we will have 80% power to detect the difference between Direct Training and Local Supervision when the standardized change for the Local Supervision strategy is ≥ 1.01–1.13.

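### The flat 0.025 per primary contrast is valid but needlessly conservative for a graded hypothesis; Holm raises the chance of showing both steps from about 61% to 74% at no cost in alpha or sample size

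*Protocol article*

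**What the plan says.** In the protocol article, the section Provider implementation fidelity outcome analyses fits a mixed model to the primary outcome, provider fidelity at 8 months. A robust score test is then applied to the time-by-strategy terms for the three arms. The error rates for this are fixed in the same place: "with a 0.05 overall Type I error rate, and a 0.025 error rate for each of the two primary strategy comparisons".

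The Sample size justification beneath it takes as its null hypotheses "no difference between Materials Only and Direct Training and between Direct Training and Local Supervision in a cluster trial". It sets the level this way: "With a 0.025 Type I error rate, allowing for two primary comparisons between the three strategies". It reports 80% power for an effect of d = "0.34–0.46 on the 8-month change of the primary outcome, assuming a between-center ICC ≤ 0.1".

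The Background states the hypothesis that "these three additive training implementation strategies will predict respective graduated increases in implementation success". It spells this out as Local Supervision above Direct Training and Direct Training above Materials Only.

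**The concern.** The hypothesis has two steps and both must be shown before the ordering of all three strategies is demonstrated. A flat Bonferroni split suits a claim that at least one contrast differs. When both must succeed it is at its weakest, because the second contrast still faces 0.025 after the first has already been rejected.

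The stated 80% applies to each contrast separately. A reader could take it as the chance of confirming the graded hypothesis, which is lower. What is at stake is efficiency: a trial of 90 centers may show one step and miss the other under a rule that is stricter than error control requires.

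**Working it through.** **Inputs from the article.** 90 centers randomized 1:1:1, so 30 per arm; about six providers per center; 0.025 per contrast; 80% power; between-center ICC up to 0.1; Direct Training mean change 0.14 with variance 0.0439.

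**Assumptions.** Two-sided tests (the article does not say), equal arms, large-sample normal theory.

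**1. Reproduce the plan's own figures.**
- Alpha: 0.025 + 0.025 = 0.05, as stated.
- Standardized change: 0.14/√0.0439 = 0.67, as stated.
- Detectable effect: d = (z₀.₉₈₇₅ + z₀.₈₀) × √(2·DE/(30·6)), with DE = 1 + 5·ICC and z₀.₉₈₇₅ + z₀.₈₀ = 2.241 + 0.842 = 3.083.
  - ICC 0.01: 3.083 × √(2.10/180) = 0.333, or 0.340 with a t reference on 58 df. This matches the lower end, 0.34.
  - ICC 0.1: 3.083 × √(3.00/180) = 0.398, or 0.407 with t. The upper end, 0.46, is reached with about 30% provider dropout (0.456 with t). That dropout figure is my assumption.

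The power calculation therefore fits a two-sided 0.025 per contrast, the same level as the analysis.

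**2. Correlation of the contrasts.** Both use the Direct Training arm, with opposite signs. If each arm mean has variance v, each contrast has variance 2v and their covariance is −v, so the correlation is −v/2v = −0.5.

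**3. Both contrasts under the flat rule.** Let each standardized contrast have mean 3.083, which gives 80% power at 0.025. Then P(both) = 0.80 + 0.80 − 1 + P(neither). In 2,000,000 simulated trials at least one contrast is significant in 0.9915, so P(neither) = 0.0085 and P(both) ≈ 0.608.

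**4. Both contrasts under Holm.** Holm rejects both when both p-values are at most 0.05 and at least one is at most 0.025.
- Power of a single contrast at 0.05: Φ(3.083 − 1.960) = 0.869.
- Both at 0.05: at least 0.869 + 0.869 − 1 = 0.738; simulated 0.740.
- Adding the requirement that one reaches 0.025: simulated 0.738.
- Power per contrast under Holm: simulated 0.86.

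**5. Range of true effects (simulated).**

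| True steps | Both: flat | Both: Holm | Direct vs Materials: flat | Direct vs Materials: Holm |
|---|---|---|---|---|
| Both at planned effect | 0.61 | 0.74 | 0.80 | 0.86 |
| Both at three quarters | 0.20 | 0.32 | 0.53 | 0.59 |
| Both at half | 0.02 | 0.04 | 0.24 | 0.25 |
| Only Direct vs Materials real | not applicable | not applicable | 0.80 | 0.80 |

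**6. Error control.** With no true difference, Holm makes a first rejection exactly when the flat rule makes one, so the family-wise error is the same: 0.047 simulated. With one real step at the planned effect, the other contrast is falsely rejected in 0.025 under the flat rule and 0.043 under Holm, still below 0.05.

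**The case against.** The strongest reply is that nothing stated is wrong. Bonferroni is valid, needs no ordering, and matches the level used for sample size, so preferring Holm is a matter of taste. The validity part stands in full. The matter-of-taste part does not: Holm rejects everything the flat rule rejects and sometimes more, with the same bound on family-wise error, so on decisions there is no trade-off.

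A second reply is that the article claims 80% per comparison only. The Background hypothesis also covers many outcomes and time points, and it is not a formal success rule for 8-month fidelity. That is fair. The 61% is therefore an unreported companion figure and does not correct the 80%. But the ordering of three strategies cannot be shown on the primary outcome without both contrasts.

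A third reply is that if the only claim were that both steps hold, each could be tested at 0.05 unadjusted, with 74.0% power. That is true, but it would leave single-step claims unprotected. Holm reaches 73.8% and keeps them.

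A reader might also infer something stronger: that a three-strategy test at 0.05 competes with the contrasts over whether the trial is positive, that multiplicity is paid for twice, or that Type I error is inflated. The phrase "assess whether the interaction terms are significantly different across the three strategies" allows a separate overall test to be read into the sentence. The sample size text, however, names only the two adjacent contrasts and explains 0.025 as the allowance for them. The natural reading is a family-wise 0.05 split in two, with the contrasts deciding. On that reading there is no conflict and multiplicity is paid for once. Inflation (0.061 in the same simulation) would need a significant overall test to count as success by itself, which the article does not say. The exact role of an overall test can properly be left to an analysis plan that is not shown.

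**Conclusion.** The point holds as a free improvement in efficiency, not as an error. The flat 0.025 rule controls family-wise error and supports the stated 80% per contrast. It is still uniformly less powerful than Holm. With both steps at the planned detectable effect, Holm raises the chance of showing both by about 13 percentage points (61% to 74%) and power per contrast by about 6 points (80% to 86%). The gain shrinks when the steps are smaller and is negligible when only one step is real.

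These figures rest on equal arms, two-sided tests, normal theory and a contrast correlation of −0.5; values for a robust score test with 90 centers would differ slightly. An unseen analysis plan does not remove the point, because the article itself fixes the 0.025.

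**What to change.** In Provider implementation fidelity outcome analyses, replace the fixed level for each contrast with Holm: test the smaller of the two p-values at 0.025 and, if it is significant, test the other at 0.05, for a family-wise rate of 0.05. Say that full support for the graded hypothesis on the primary outcome requires both contrasts in the predicted direction.

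In the Sample size justification for that outcome, keep the 0.025 calculation as a conservative per-contrast figure. Add the joint power (about 74% under Holm, 61% under the present rule) with its assumptions.

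As a minor clarification, state that claims rest on the two contrasts and that any three-strategy score test is descriptive.

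The cost is two or three sentences, with no added participants, tests or alpha. Confidence intervals at 97.5% per contrast remain valid but may not match a Holm rejection made at 0.05, so the report should say which intervals it shows. The change should be recorded before primary results by arm are seen, and the analysis plan should carry the same rule.
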